## Abstract

**Background:**

CenteringPregnancy (CP) is a multifaceted group based care-model integrated in routine prenatal care, combining health assessment, education, and support. CP has shown some positive results on perinatal outcomes. However, the effects are less obvious when limited to the results of randomized controlled trials: as there are few trials and there is a variation in reported outcomes. Furthermore, former research was mostly conducted in the United States of America and in specific (often high risk) populations. Our study aims to evaluate the effects of CP in the Netherlands in a general population of pregnant women (low and high risk). Furthermore we aim to explore the mechanisms leading to the eventual effects by measuring potential mediating factors.

**Design:**

We will perform a stepped wedge cluster randomized controlled trial, in a Western region in the Netherlands. Inclusion criteria are <24 weeks of gestation and able to communicate in Dutch (with assistance). Women in the control period will receive individual care, women in the intervention period (starting at the randomized time-point) will be offered the choice between individual care or CP. Primary outcomes are maternal and neonatal morbidity, retrieved from a national routine database. Secondary outcomes are health behavior, psychosocial outcomes, satisfaction, health care utilization and process outcomes, collected through self-administered questionnaires, group-evaluations and individual interviews. We will conduct intention-to-treat analyses. Also a per protocol analysis will be performed comparing the three subgroups: control group, CP-participants and non-CP-participants, using multilevel techniques to account for clustering effects.

**Discussion:**

This study contributes to the evidence regarding the effect of CP and gives a first indication of the effect and implementation of CP in both low and high-risk pregnancies in a high-income Western society other than the USA. Also, measuring factors that are hypothesized to mediate the effect of CP will enable to explain the mechanisms that lead to effects on maternal and neonatal outcomes.

**Trial registration:**

Dutch Trial Register, NTR4178, registered September 17^th^ 2013.

## Background

In the Netherlands, perinatal mortality and morbidity is relatively high compared to other European countries. One in six children is born with health problems, defined as congenital anomalies, preterm birth, low birth weight and a low Apgar score [1]. Risk factors for adverse perinatal outcomes are amongst others life style (e.g. in the Netherlands 11% of the women with a lower education level smoke during pregnancy [2]), psychological issues [3], work related risks [4], medication use [5] and chronic illnesses [6]. In addition, perinatal outcomes are worse for ethnic minorities (non-Western ethnicity) [7, 8] and for Western women living in deprived urban areas [9, 10]. Influencing these risk factors could lower the perinatal morbidity rate. Often, however, interventions targeted at the general population do not reach (ethnic) minorities and have limited effects on health behavior [11–13].

In 2012, CenteringPregnancy (CP) was introduced in the Netherlands [14]. CP, developed in the United States of America (USA), is a model of prenatal group based care, within which one-to-one visits are being replaced by group consultations [15]. CP combines the three major components of care – health assessment, education, and support. The group based character of CP allows more time for self-management, education, skill building, and caregiver-patient interaction [16–18]. In addition, the group process can strengthen patient’s self-efficacy by vicarious learning and modeling by seeing others successfully overcoming barriers and accomplishing desired behavioral changes [19–22]. Next, CP is integrated in the Dutch routine prenatal care, which is freely accessible to all women in the Netherlands (in 2014 173,544 women received prenatal care [23]). The integrated character improves the reach of the preventive activities that are embedded in CP, as was shown by a former Dutch study concluding that women from an ethnic minority group evaluated a prevention program that was fully integrated in routine midwifery care as highly acceptable and satisfactory [24]. In summary, CP has the potential to effectively influence the risk factors for adverse perinatal outcomes to reach high-risk groups.

Research on CP has shown some positive effects: amongst others on health literacy [25, 26], preparedness for labor and birth [17], and initiating breastfeeding [17, 27]. Women reported receiving more social support [28, 29], and were more satisfied with provided care [17, 28–30]. Moreover, the number of preterm births significantly decreased in a high-risk population, the mean birth weight increased and the number of women who received substandard care was reduced [17, 29].

However, a part of the evidence is derived from non-randomized studies. The evidence from randomized controlled trials (RCT) is less obvious, which is due to the limited number of RCT’s on prenatal group-based care and the variation in the reported outcomes [17, 27, 30, 31]. Recently, Caitlin et al. concluded that additional research is required to assess the effects of prenatal group-based care models, such as CP, on neonatal and maternal outcomes [26]. Furthermore, most results of the effect of CP originate from experimental studies conducted in high-risk populations and in the USA [17, 29, 31–34]. It is unknown what the effect of CP is in a different maternity healthcare system and in the general population.

The aim of the present study is to evaluate the effects of CP in the Netherlands in primary health care (low risk population) as well as in hospital based care (moderate to high risk population) on neonatal and maternal health outcomes, health behaviors and psychosocial outcomes. The effectiveness of CP will be established by comparing the outcomes in the intervention group (prenatal care within the CP model) and the control group (usual individual care). Primary hypotheses are that in comparison to the control group, the intervention condition will lead to better neonatal and maternal outcomes. Secondary hypotheses are that the effect on the outcome variables is mediated by (changes in) health literacy, self-regulation, health behavior, health care utilization as well as level of group cohesion and level of implementation.

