#### Intervention group

Within the intervention period, pregnant women are offered perinatal care in the CP model. In the CP model traditional prenatal care with one-to-one visits with a perinatal care provider is replaced by the use of a group model [35]. Care is provided by a midwife or an obstetrician (facilitator) and a co-facilitator to groups of eight to twelve women of similar gestational age. Groups meet eight to ten times during pregnancy at the usual scheduled visits, with sessions running for 90 to 120 min. The usual prenatal health assessment is integrated with information, education and peer support. All involved care providers will be trained by licensed trainers to perform CP. The intervention period begins when the center starts to recruit for their first CP group, after the randomized time point. All women included in the study during this period will be part of the intervention group. In addition to the study information, participants will be informed about CP at their first prenatal consultation and will be given the choice to participate in CP. Women that do not participate in CP will receive usual individual care, resulting in two sub-groups within the intervention group. See Fig. 1.

We will use data from the Perined database. The Perined database contains linked and validated routine care information concerning pregnancy, delivery, (re)admissions and pregnancy outcomes [36]. Data are routinely and separately registered by midwives, obstetricians, general practitioners and paediatricians/neonatologists. For this study, the Perined data will be complemented with data from the questionnaires to be completed by participating women at four time points: Table 1 provides an overview of the timing of the different items. Reminders will be sent after 1, 2 and 3 weeks and participants will be reminded by their care provider. Finally, we will use implementation data from CP-group-evaluations and qualitative data from semi-structured interviews with care providers. Outcome measurements are described below. More details on instruments used in the questionnaires are provided in Table 2.

**Table 1 Tab1:** Overview of items in the questionnaires at four measurement time points

T1, inclusion (8–12 weeks of GA)	T2 (28 weeks of GA)	T3 (36 weeks of GA)	T4 (6 weeks postpartum)
Basic characteristics, current weight	Life style Knowledge (2)	Life style (3), medication use (2)	Life style (4), prenatal and perinatal health care use (2)

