### Statistical issues

#### Sample size calculation

A minimal sample of 600 pregnant women in both the intervention and control condition is needed to be able to accept with 95% confidence and an upper confidence limit less than 1.85, that after the intervention has been implemented, there is at least no significant difference in infant morbidity (using 14% of infant morbidity as outcome) between CP and individual care. This sample size is also largely sufficient to find amongst others a difference in prenatal care satisfaction or in proportion of breastfeeding comparable to Ickovics et al, with an α of 0.05 and a power of 0.90 [17]. We will account for a 20% loss to follow-up and aim to include in total 1600 women (800 in both conditions).

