#### Data analysis

Data entry will be automatic by using a secured online survey system or (in case of hard copy) scanned and checked using the Teleform software. Data will be stored in a digital data base only accessible to the researchers. Before analysis, all data will be cleaned improving data quality.

We will conduct intention-to-treat analyses to compare the primary and secondary outcomes of the control group with those of the complete intervention group. Also a per protocol analysis will be performed comparing the outcomes of the three subgroups (see Fig. 1): control group (1), CP-participants (2) and non-CP-participants (3). Analyses will be descriptive and inferential (univariate and multivariate), and we plan to perform multilevel techniques to account for the clustering effect among participants in centers and CP-participants in CP-groups. The analysis of the implementation data and health care use will be descriptive. The relation between the degree of implementation and primary and secondary outcomes will be analyzed using multi-level analysis. Furthermore, the interviews with care providers will be conducted using a topic list based on the results of the analysis of the implementation data. They will be transcribed and qualitatively analyzed using a framework approach.

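### The objective and the 1.85 no-difference criterion are worded as CP versus individual care, but the main comparison estimates the effect of introducing and offering CP, and non-uptake makes that criterion easier to meet

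*Protocol article*

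**What the plan says.** The Protocol article describes the contrast in two ways.

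- **As care received.** The aim in the Background rests on "comparing the outcomes in the intervention group (prenatal care within the CP model) and the control group (usual individual care". Under Sample size calculation, 600 women per condition are said to allow the trial "to accept with 95% confidence and an upper confidence limit less than 1.85" that "there is at least no significant difference in infant morbidity (using 14% of infant morbidity as outcome) between CP and individual care".
- **As care offered.** Under Intervention group, "All women included in the study during this period will be part of the intervention group", each woman is given the choice, and "Women that do not participate in CP will receive usual individual care, resulting in two sub-groups within the intervention group". Under Data analysis, the intention-to-treat analysis will "compare the primary and secondary outcomes of the control group with those of the complete intervention group".

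A further analysis is planned: "Also a per protocol analysis will be performed comparing the outcomes of the three subgroups", namely control, CP participants and non-participants. The article gives no expected uptake. Under Process outcomes, the percentage of women who start CP is to be monitored.

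**The concern.** The group that the Background describes as receiving CP contains women receiving the comparator. The sample size section counts women by condition, but words its conclusion for CP itself.

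In a test for benefit this would be a minor looseness, because women who decline CP pull the estimate towards no effect and so work against the claim. The sample size, however, is justified by an upper limit that must stay below 1.85. For that criterion the same pull works in favour of the claim. If the sample size wording is followed, a result showing that offering CP leaves infant morbidity within the limit would be reported as reassurance about CP itself. The intention-to-treat contrast does not give that reassurance unless uptake is close to complete.

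**Working it through.** **Inputs from the Protocol article (Sample size calculation):** 14% infant morbidity, 95% confidence, upper limit 1.85, 600 per condition, 20% loss, 800 recruited per condition. The article does not say whether 1.85 is an odds ratio or a risk ratio, and gives no power for this criterion.

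**Assumed:** uptake u; women who decline CP stay at 14%; women who accept and women who decline have equal baseline risk; clustering ignored; two-sided 95% interval.

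**1. The plan's own figure.** With no true difference and an odds ratio margin, n per group = 2(z_a + z_b)² / [p(1−p)(ln 1.85)²], with p = 0.14 and z_a = 1.96. This gives 345, 462, 571 and 605 at 80%, 90%, 95% and 96% power. The risk ratio version, 2(z_a + z_b)²(1−p) / [p(ln 1.85)²], gives 255, 342, 422 and 447. So 600 cannot be firmly reproduced, but it exceeds the individually randomised requirement at 80% to 95% power and is not shown to be wrong.

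**2. Place CP exactly at the limit.** Odds = 1.85 × 0.14/0.86 = 0.3012, so the risk under CP is 0.3012/1.3012 = 23.1%.

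**3. Mix in the women who decline.** Risk in the complete intervention group is q = u × 0.2315 + (1 − u) × 0.14. At u = 0.5, q = 0.1857. The odds ratio against control is (0.1857/0.8143)/(0.14/0.86) = 1.40.

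**4. Chance that the upper limit is below 1.85.** SE = √[1/(600 × 0.14 × 0.86) + 1/(600 × q(1−q))], and the probability is Φ[(ln 1.85 − ln OR)/SE − 1.96]. At u = 0.5, SE = 0.1577, and (0.6152 − 0.3373)/0.1577 − 1.96 = −0.20, so the probability is 42%.

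| Uptake (assumed) | Expected intention-to-treat OR | P(upper limit < 1.85), OR scale | Same check, CP at RR 1.85, RR scale |
|---|---|---|---|
| 100% | 1.85 | 2.5% | 2.5% |
| 70% | 1.57 | 18% | 22% |
| 50% | 1.40 | 42% | 52% |
| 30% | 1.24 | 71% | 82% |

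**5. Does also requiring no significant difference change this?** The upper limit is below 1.85 when the estimated log odds ratio is below 0.6152 − 1.96 × SE. The difference is non-significant on the harm side when that estimate is below 1.96 × SE. At 50% uptake these thresholds are 0.306 and 0.309, so the two conditions nearly coincide and 42% stands. At 30% (SE 0.1606) they are 0.300 and 0.315, and 71% stands. At 70% (SE 0.1553) they are 0.311 and 0.304, which moves 18% to 17%.

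**6. Women available for the three-subgroup analysis.** After 20% loss, 800 × 0.8 = 640 remain, so CP participants number 640 × u: 448, 320 and 192 at 70%, 50% and 30% uptake. The 600 per condition was not set for this comparison.

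**The case against.** Much of the case on the other side stands.

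- **The design is disclosed.** The Abstract and the Intervention group section state the choice, the Data analysis section defines the intention-to-treat contrast, and the Discussion names self-selection as a limitation, plans correction for basic characteristics and calls the trial pragmatic. The primary hypotheses in the Background are worded for the intervention condition. The comparison is therefore defined, and the fault lies in how its conclusion is worded.
- **Intention-to-treat is the proper analysis for the offer.** A reader might infer that the main comparison is invalid or cannot inform on CP. The documents do not support that. A benefit found there would show that introducing and offering CP works, and non-uptake is conservative for that hypothesis.
- **The number of CP participants is not known to be below 600.** A reader might assume it is. With 800 recruited, 94% uptake after 20% loss, or 75% uptake with no loss, would reach 600.
- **A fixed bound for women who receive CP cannot be read off.** It is tempting to say that a limit of 1.85 for the offer excludes only a risk ratio above 1 + 0.85/u for CP, for example 1 + 0.85/0.5 = 2.7. That applies only to an observed limit of exactly 1.85. It also needs no spill-over, whereas the Design section expects training to affect non-CP consultations, and equal baseline risk, whereas the Discussion allows for selection.
- **Expected uptake** may properly sit in a fuller document, so its absence is not a fault here.

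The planned per protocol analysis does not answer the point. It compares self-selected women, and correction for measured characteristics deals only with what was measured.

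**Conclusion.** The point holds as an inconsistency of wording that matters for one claim. The aim and the 1.85 criterion name CP against individual care, while the main analysis compares all women offered CP with control. For the no-difference criterion, if declining women are unaffected, any uptake below 100% raises the chance of meeting the limit when CP itself sits at it: from 2.5% to about 18%, 42% and 71% at 70%, 50% and 30% uptake on the odds ratio scale. These figures rest on assumed uptake, unaffected women in individual care, equal baseline risk and no clustering, so they show direction and rough size only. Neither the sample of 600 nor the choice of intention-to-treat is shown to be wrong.

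**What to change.** In the Background aim and under Sample size calculation, restate the objective and the 1.85 criterion as the effect of introducing and offering the choice of CP, compared with individual care only. Draw no conclusion of no difference between CP and individual care from the intention-to-treat result, and report that result beside the observed uptake, which is already to be monitored. If an implied bound for women who receive CP is given, show it only as a sensitivity illustration that states the no-spill-over and equal-baseline-risk assumptions.

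This needs no additional women or data. The cost is that the stated claim becomes narrower and less favourable.

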## Methods

### Design

This study will be performed in thirteen midwifery practices (primary care, low-risk population) and two hospitals (secondary care, moderate to high-risk population) that do not yet offer CenteringPregnancy within the region ‘northern South-Holland’ (an urban – sub-urban setting). A stepped wedge cluster randomized controlled trial design is chosen for several reasons. Firstly, randomization at individual level is not appropriate, as training professionals in CP will most probably also affect the non-CP consultations. Secondly, since midwifery care in the Netherlands is subjected to marketing forces, cluster randomization is expected to result in unfair competition between independent centers operating in the same region. Within the chosen design, all clusters (midwifery practice or hospital) start to collect control data at the same time (control period). Clusters will subsequently implement the intervention at a different, randomly selected time point and will then start to collect intervention data (intervention period). For this study, we will divide all fifteen centers into three groups and will randomly assign each group to one of three time points (steps) at which they will start to implement the intervention, with a between-step period of 3 months.

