## Discussion

Former research has shown a positive effect of CP, including a higher birth weight and more prenatal care satisfaction, however the findings were inconsistent [17, 26, 27, 30, 31]. Furthermore, due to differences in population characteristics and health care system, previous findings cannot be directly extrapolated to the Dutch setting. Our study aims to contribute to the evidence regarding the effect of CP and will give a first indication of the effect and implementation of CP in a Western high-income society other than the USA. Also, by measuring factors that are hypothesized to mediate the effect of CP, we aim to be able to explain the mechanisms that lead to eventual found effects on maternal and neonatal outcomes.

A strength of our study lies in the stepped wedge cluster design. In this design, participating practices are randomly assigned to the period in which they will start providing CP and will function as their own control group before implementing CP. Also, it allows to take into account time effects. Another strength of the study is the use of routine data to assess several neonatal and maternal outcome measures.

One limitation however is the fact that centers are not yet trained in CP and that it takes some time to implement, which may lead to less model fidelity and smaller effect sizes. Fidelity to facilitate group processes in CP and content fidelity are known to associate with significant reductions in preterm birth and intensive utilization of care [58]. To gain more insight in the effects of fidelity of the model as provided by health care providers we will collect data on process and implementation, and will relate it to the effects of CP. The possibility of selection bias by letting women choose between CP or individual care is another limitation of our study. To be able to estimate the degree of selection bias, we will collect numerous demographic and psychosocial data of both groups in the intervention period (CP-participants and Non-CP-participants), also allowing us to correct for differences in basic characteristics. In addition, we will perform an intention-to-treat analysis, as well as a per protocol analysis. Differences in results of both analyses will provide an indication of assumed selection bias.

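### The stated allocation does not keep the two hospitals on different steps; if they share one, the hospital effect is separable from calendar time only by borrowing the midwifery practices' trend

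*Protocol article*

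**What the plan says.** The aim, in the Background of the protocol article, is to evaluate CenteringPregnancy (CP) "in primary health care (low risk population) as well as in hospital based care (moderate to high risk population". The Discussion part of the abstract likewise promises a first indication of the effect in low- and high-risk pregnancies.

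Under Design, the clusters are "thirteen midwifery practices (primary care, low-risk population) and two hospitals (secondary care, moderate to high-risk population". On allocation the article says: "we will divide all fifteen centers into three groups and will randomly assign each group to one of three time points (steps", "with a between-step period of 3 months". Before that, "all clusters (midwifery practice or hospital) start to collect control data at the same time (control period". Group sizes, the way centres are put into groups and any role for setting are not described.

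Under Data analysis, the intention-to-treat analysis will "compare the primary and secondary outcomes of the control group with those of the complete intervention group", using "multilevel techniques to account for the clustering effect among participants in centers and CP-participants in CP-groups". No hospital-only analysis and no setting-by-treatment term is described. The main Discussion section counts it as a strength of the design that "it allows to take into account time effects".

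**The concern.** A stepped wedge design separates treatment from time because, in the middle periods, some clusters have crossed over and others have not. For the hospitals this depends on two clusters only. If both cross over together, no hospital is ever in the control condition while the other is in the intervention condition. Within the hospitals, the comparison is then an uncontrolled before-after one. Having each centre serve as its own control does not help, because both hospitals change condition at the same calendar time.

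What is at stake is the moderate-to-high-risk part of the aim. A hospital effect could still be computed, but its adjustment for time would come entirely from low-risk practices. Referral patterns, case mix and registration practice may drift differently in the two settings, and the hospital data could not show whether they had.

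**Working it through.** The article gives no probability or identifiability figure on this point, so there is nothing of its own to reproduce first.

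**Inputs from the article (Design):** 13 practices, 2 hospitals, 15 centres, 3 groups, 3 steps, all clusters starting in the control condition together.

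**Assumptions:** groups formed at random; five centres per group, with other sizes also tried; four periods (one all-control period, then one after each step). The article fixes only the interval between steps, so the four equal periods are a working simplification.

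**1. Probability of a shared step.** For group sizes n1, n2, n3:

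P(same step) = [C(n1,2) + C(n2,2) + C(n3,2)] / C(15,2), with C(15,2) = 105.

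- 5/5/5: (10 + 10 + 10)/105 = 30/105 = 28.6%
- 4/5/6: (6 + 10 + 15)/105 = 31/105 = 29.5%
- 4/4/7: (6 + 6 + 21)/105 = 33/105 = 31.4%
- 3/6/6: (3 + 15 + 15)/105 = 33/105 = 31.4%
- 3/5/7: (3 + 10 + 21)/105 = 34/105 = 32.4%
- Groups composed deliberately: 0% or 100%, depending on whether the hospitals were placed apart or together.

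**2. Can the hospital effect be estimated?** The cluster-by-period model has 15 centre effects, 3 period contrasts and separate CP effects for hospitals and practices.

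- *Period effects common to both settings:* 15 + 3 + 2 = 20 parameters. The rank is 20 in every allocation, so the hospital effect is estimable even with a shared step.
- *Setting-specific period effects:* 3 more contrasts, 23 parameters. With a shared step the rank is 22 and the hospital effect is not estimable. With different steps the rank is 23 and it is estimable.
- The midwifery effect is estimable in every case.

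The reason is simple. If both hospitals cross over at the same step, the hospital intervention indicator equals the sum of the hospital period indicators from that step onward.

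**3. Precision.** Variances are in units of the variance of one cluster-period mean, with cluster-periods taken as equally precise and independent given the centre effect.

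- *Common period effects:* hospital variance 0.67 to 0.86 with a shared step, 0.74 to 0.83 with different steps. Under this assumption, splitting the hospitals brings no consistent gain.
- *Setting-specific period effects, different steps:* the estimate is a contrast of the between-hospital difference in the k periods when only one hospital is on CP against the other 4 - k periods. Its variance is 2 × [1/k + 1/(4 - k)].
  - Steps 1 and 2, or 2 and 3 (k = 1): 2 × (1 + 1/3) = 2.67
  - Steps 1 and 3 (k = 2): 2 × (1/2 + 1/2) = 2.00
  - Shared step (k = 0): undefined, in agreement with the rank result.
- *Midwifery effect in the same model:* about 0.28. The ratios are 2.00/0.283 = 7.1 and 2.67/0.277 = 9.6.

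**The case against.** The strongest reply is that this is a condensed journal article. It says the centres are divided into groups and the groups are then randomised; only the second act is called random. Whether setting played a part in forming the groups is not stated, and such detail is often left to the full protocol. This stands in part. A reader might infer that allocation was definitely unrestricted, or that the chance of a shared step is 29% without conditions, and the text supports neither. What remains is that the allocation as described pools two unlike settings and that a better allocation is available at no cost.

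A second reply is that the hospital effect is not lost even with a shared step. That is right if the time trend is common to both settings: the model has full rank and precision is about the same as with split hospitals. A reader might conclude that the effect is flatly inseparable from calendar time, but that holds only if hospitals may have their own trend. A common trend between low-risk practices and moderate-to-high-risk hospitals is nevertheless a strong assumption, and with a shared step the data could not test it in the hospitals.

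A third reply is that the planned analysis is pooled and no separate hospital estimate is promised. This also stands. A reader might think the primary comparison is threatened. It is not, because the pooled effect is identified under every allocation. The point concerns only what the trial can say about the hospital setting, which is named in its aim.

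Finally, two hospitals are few, and splitting them does not create power. This is correct and limits what the change can deliver.

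**Conclusion.** The point holds as a free improvement to the allocation, not as a flaw in the primary analysis. As described, nothing prevents both hospitals from sharing a step. The probability is 28.6% under random groups of five and 29.5% to 32.4% for the unequal random groups tried. It is 0% or 100% if the groups are composed deliberately. Given a shared step, the hospital effect is confounded with calendar time unless hospitals are assumed to follow the practices' trend (rank 22 of 23 with setting-specific periods, 20 of 20 with common periods).

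The result rests on four periods, on random group formation for the probabilities, and on equally precise, independent cluster-periods for the variances. The documents do not support saying that the trial cannot estimate a hospital effect at all, that its pooled result is unidentified, or that the full protocol contains no restriction.

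**What to change.** - **Allocation:** draw two different steps at random for the two hospitals, then randomise the thirteen practices to the remaining places (4, 4 and 5 if each step takes five centres). State the group sizes and that the groups are formed at random. The probability of a shared step becomes zero.
- **Analysis:** in any hospital-specific estimate, or as a sensitivity analysis, include setting-by-period terms. A setting main effect alone shifts the level of the outcome and leaves the shared time trend in place.
- **Interpretation:** say that a hospital-specific estimate rests on two clusters, with a variance roughly 7 to 10 times that for the practices, and is a first indication only.
- **If allocation has already taken place:** report the steps the hospitals received. If they coincide, state that any hospital estimate relies on a time trend shared with the practices.

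The cost is a sentence on restricted randomisation and a sentence or two on analysis. The number of centres, the sample size and the timetable stay as they are.
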